### Randomisation

Following consent, eligible patients will be randomised in a 1:1 ratio to open or laparoscopic resection using a central computer system at the Oncology Clinical Trials Office. Simple randomisation will be used for the first 50 patients then minimization with a random element (0.8) [25]. The stratification factors used in the minimization are hospital, cancer site (colon/rectum) and age (<66 years, 66–75 years, >75 years). To facilitate blinding of outcome observers the randomisation allocation will be sent directly to the patient’s surgeon via email and will not be made available to the site staff member completing the randomisation process.

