### Statistical analysis

Sample size: The original sample size calculation required 266 patients (133 per treatment arm) to allow 90% power to detect a difference in the primary outcome of fatigue (as measured by physical fatigue domain of the MFI-20) of 0.45 standard deviations at p = 0.05 (two-sided). This includes a loss to follow up of 15% and a conversion rate of 8% from laparoscopic to open surgery. Following slower than expected recruitment the power was lowered to 80% in order to complete the study in a timely manner. With all other variables remaining the same the subsequent sample size of 202 (101 per treatment arm) is required. Additionally the study is powered to detect a 3 day difference in hospital stay at 80% power and p = 0.05 (two-sided).

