### Analysis

All analyses will be on an intention-to-treat basis.

The primary outcome will be physical fatigue as measured by the physical fatigue domain of the MFI-20 at four weeks post operatively. If the primary outcome is normally distributed it will be compared using a *t*-test, ANCOVA adjusting for the minimization factors (primary analysis) and ANCOVA with further adjustment for prognostic factors.

Physical fatigue will also be compared at three and six months, the remaining quality of life variables at 4 weeks, 3 and 6 months, and the cosmetic outcome at 6 and 12 months, using the same analyses as for the primary outcome. Physical fatigue will be adjusted for the level of physical fatigue prior to surgery. The other measures of fatigue will also be reported.

For all continuous outcome variables, if there is severe departure from Normality the first approach will be transformation. If the data cannot be transformed to Normality, a Mann–Whitney test will be used. In the latter case no adjustment will be made for the minimization or prognostic factors.

Hospital stay will be compared using Kaplan Meier plots and log rank tests. The complications, re-operation and re-admission data will be binary and will hence be compared between the randomisation groups using a chi square test (or Fisher exact test if the data is sparse).

Quality of Life assessments at 4 weeks as measured by the SF-36 will be analysed as suggested in the SF-36 manual, comparison between treatments will use *t*-test and ANCOVA to adjust for prognostic factors. Mixed-effects models of repeated measures will be used to evaluate longitudinal comparisons (4 weeks, 3 months and 6 months).

The other four domains of the MFI will be analysed in the same way as the physical fatigue domain specified in the primary analysis.

The comparison between treatment groups of standardised performance indicators will use t-tests and ANCOVA adjusting for prognostic factors and baseline.

The tumour stage, quality of surgery grade, the physical measurements and the frequency of Dukes’ C2 cases will be compared between groups.

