## Discussion

The EnROL trial has been set up to examine the hypothesis that laparoscopic surgery improves outcome when compared to open surgery for colorectal cancer resection, even when both methods are optimized within an ERP. Prior to 2011 there had only been two small studies examining this issue [10,19] and they reported conflicting results. Other trials reporting an improvement in clinical outcome following laparoscopic surgery did not use an enhanced recovery programme to optimize the open group [1,2,4].

In 2011 the LAFA trial [35] published outcomes comparing the two approaches to surgery +/− an ERP. In this study of patients having segmental colectomy, total hospital stay was reduced following laparoscopic surgery when compared to open surgery. There are significant differences between the EnROL and LAFA trials that warrant continuation of EnROL. The EnROL trial only involves very experienced laparoscopic surgeons; it will include patients with rectal carcinoma; it will not include patients with benign diagnoses; and there will be no attempt to randomise between ER care and non ER care, as happened in the LAFA trial.

The involvement in this trial of surgeons experienced in laparoscopy is important as it minimises the % conversion rate to open surgery, thus providing a more homogeneous laparoscopic group of patients (given the intention to treat analysis) and increasing the potential to demonstrate differences in outcome. The choice of 100 prior laparoscopic resections to enable surgeons to contribute to EnROL is both intuitive and based on data from studies examining the acquisition of surgical competence with this approach [36]. Rectal carcinoma has been included in the EnROL trial as rectal resection is often more difficult than colonic surgery and also more demanding laparoscopically. As a result only one large randomised trial has been reported to date examining outcomes following resection of both high and low rectal cancers [6]. Generally hospital stay following rectal surgery is longer than after colonic surgery and therefore the potential to improve outcome after rectal surgery is greater, assuming laparoscopy decreases complications.

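### Hospital stay is to be tested by a log-rank test with no stated use of the minimisation factors, so it is conservative to the extent that those factors predict stay

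*Protocol article*

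**What the plan says.** All places are in the protocol article.

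- **Randomisation.** "The stratification factors used in the minimization are hospital, cancer site (colon/rectum) and age" (three bands). The first 50 patients are allocated by simple randomisation, and later patients by minimisation with a random element of 0.8.
- **Analysis, primary outcome.** The primary analysis of physical fatigue at four weeks is an ANCOVA that includes the minimisation factors.
- **Analysis, stay.** "Hospital stay will be compared using Kaplan Meier plots and log rank tests". Nothing is said about strata or covariates.
- **Analysis, binary outcomes.** Complication, re-operation and re-admission data "will hence be compared between the randomisation groups using a chi square test (or Fisher exact test if the data is sparse".
- **Statistical analysis, sample size.** Besides the fatigue calculation, the trial is said to have 80% power, at two-sided 0.05, for a 3-day difference in stay. No standard deviation or event model is given.
- **Discussion.** "Generally hospital stay following rectal surgery is longer than after colonic surgery".
- **Analysis, other continuous outcomes.** One sentence gives the remaining quality-of-life variables the same analyses as the primary outcome. A later SF-36 sentence names only prognostic factors. The ANCOVA for the performance indicators names prognostic factors and baseline.

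**The concern.** Minimisation makes the arms alike on hospital, cancer site and age. The log-rank test computes its variance as if that had not been done. If the factors predict stay, part of the variation it counts as chance has already been removed by design, and its type I error falls below nominal. Leaving strong predictors out of a time-to-event comparison also pulls the hazard ratio towards one, which costs power as well.

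The article accepts this logic for fatigue and does not carry it over to stay. Its own Discussion says that one of the three factors, cancer site, predicts stay. What is at stake is power for the one secondary outcome that the trial says it is powered for, in a trial where "Following slower than expected recruitment the power was lowered to 80% in order to complete the study in a timely manner".

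**Working it through.** **1. The plan's sample size.** Inputs from the sample size paragraph: an effect of 0.45 SD, two-sided alpha 0.05, and allowances of 15% for patients lost and 8% for conversions.

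n per arm = 2(z₀.₉₇₅ + z_power)² / 0.45², then divided by 0.85 × 0.92 = 0.782.

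- 90% power: 103.8, so 104; 104 / 0.782 = 132.99, or 133 per arm (266). This matches.
- 80% power, normal approximation: 77.5, so 78; 78 / 0.782 = 99.7, or 100 per arm. With the t distribution: 79 / 0.782 = 101.02, or about 101 per arm. The plan says "the subsequent sample size of 202 (101 per treatment arm) is required". This is reproduced.

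**2. The stay claim.** It cannot be reproduced without a standard deviation. Read as a comparison of means with 101 per arm, it implies SD = 3 × √(101/2) / 2.80 = 7.6 days, or 7.0 days with 101 × 0.85 = 85.85 per arm. It says nothing of the power of a log-rank test.

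**3. Simulation of the planned test.** Taken from the article: 202 patients, 12 hospitals, 1:1 allocation, 50 patients by simple randomisation and then minimisation at 0.8 on the three factors.

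Assumed, because the article gives no figures:
- hospital shares from 20% down to 2%; 35% rectal; age bands 35/35/30%
- log-normal stay rounded up to whole days, reference median 6 days, log-SD 0.6
- laparoscopic effect −0.27 on log stay (exp(−0.27) = 0.76, about 24% shorter)
- factor effects on log stay as in the table

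Each row uses 1,500 trials under the null and 1,500 under the effect. Monte Carlo standard errors are √(0.05 × 0.95/1500) = 0.6 points for type I error and √(0.8 × 0.2/1500) = 1.0 point for power (1.2 near 69%).

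The three figures in each cell are: plain log-rank / log-rank stratified by cancer site and age / Cox stratified by hospital and adjusted for site and age.

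| Factors | Hospital SD; rectal v colon; per age band | Type I error, % | Power, % |
|---|---|---|---|
| Not prognostic | 0; 0; 0 | 5.4 / 5.4 / 5.2 | 82.2 / 81.9 / 80.2 |
| Moderate | 0.15; 0.3; 0.1 | 4.3 / 4.5 / 5.8 | 79.2 / 81.1 / 80.6 |
| Strong | 0.35; 0.5; 0.2 | 2.9 / 4.0 / 5.7 | 69.3 / 74.4 / 81.9 |

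Cox minus plain log-rank: 80.2 − 82.2 = −2.0 points; 80.6 − 79.2 = +1.4 (79 v 81 in whole points); 81.9 − 69.3 = +12.6. Stratifying by site and age alone recovers 74.4 − 69.3 = 5.1 points in the strong case.

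**4. A second set of assumptions.** Open colonic median 5 days, rectal stay 1.65 times longer, log-SD 0.6, stay 22% shorter with laparoscopy. Power for plain log-rank / stratified by site / stratified by site and hospital:
- hospital SD 0.3: 65% / 69% / 74%, with type I error 3.1% / 4.5% / 5.9%
- hospital SD 0: 71% / 77% / 74%

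The direction agrees. When hospitals do not differ, crossing site with hospital gains less than site alone.

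**5. Binary outcomes.** Same allocation; assumed reference risk about 30% (logit −0.85) and treatment log odds ratio −0.8. Chi-square v logistic score test adjusted for all three factors:
- power: 66.7 v 68.7, 69.4 v 72.0 and 65.5 v 69.3, i.e. gains of 2.0, 2.6 and 3.9 points (the last from unrounded figures)
- type I error: 4.6 v 5.6, 4.6 v 5.4 and 3.8 v 5.7

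The 2.0-point gap in the first scenario, where there is nothing to adjust for, reflects the adjusted test's higher rejection rate and no real gain in efficiency.

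**The case against.** The strongest reply is that the planned tests are valid, the outcomes are secondary, and the error is towards caution. All of that stands. A reader might infer that the log-rank test risks false positives; the error runs the other way.

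The size is also open to challenge. The article gives no variance, hospital effect or rectal-to-colonic ratio, and the loss is material only if the factors are strongly prognostic. The adjusted Cox model ran at 5.2% to 5.8%, so a little of its apparent gain may come from that. This stands, and is why the size is given as a range.

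The supporting evidence is narrower than it may look. The discharge aims in Table 1 differ by whether a stoma is fashioned, which is not a minimisation factor, and put proximal rectal with colonic resection. Leave for centres to amend the recovery programme makes hospital differences plausible but does not show them. Only the Discussion's remark on rectal surgery ties a minimisation factor to stay, and it gives no size.

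An unseen analysis plan could specify strata, and a log-rank test can be stratified. But the article names its tests and deals with adjustment outcome by outcome, even saying when it is dropped, so the plain reading is an unadjusted test. How in-hospital deaths are handled, and whether a hazard ratio with its interval is reported, are details an article may leave out; their absence is no fault.

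A reader might also infer that the SF-36 analysis omits the minimisation factors. The sentence giving the remaining quality-of-life variables the primary-outcome analyses does not support that. The two statements differ and need reconciling.

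**Conclusion.** The point holds for hospital stay. The stated test ignores factors on which the arms are balanced, at least one of which the article itself says predicts stay. To the extent that they are prognostic, the test is conservative and loses power. Against an adjusted Cox model the loss runs from none (the plain test is about 2 points better if the factors do nothing), through 1 to 2 points at moderate strength, to about 13 points at strong strength, where type I error is about 3%. These figures rest on the assumed log-SD of 0.6, the assumed treatment effect and the assumed factor effects.

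Two stronger readings are not supported. One is that the 80% claim for stay is wrong: with no standard deviation stated, it can be neither confirmed nor refuted. The other is that complications, re-operation and re-admission suffer materially: the difference is 2 to 4 points at most and partly reflects the adjusted test running slightly above 5%.

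Importance is low to moderate.

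**What to change.** **Stay.** Compare time to discharge with a Cox model stratified by hospital, with cancer site and age group as covariates, and report the hazard ratio and 95% confidence interval beside the Kaplan-Meier plot. Alternatively, use a log-rank test stratified at least by cancer site. Do not stratify on all three factors at once: 12 × 2 × 3 = 72 cells for 202 patients is under three per cell. Pool small hospitals by a rule fixed before the data are seen.

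**Binary outcomes.** For consistency, logistic regression with cancer site and age group, or Mantel-Haenszel, may be used. This is optional, as the gain is small.

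**Other continuous outcomes.** Add the minimisation factors to the performance-indicator ANCOVA. Reconcile the two SF-36 statements in the Analysis section so that one covariate set applies.

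**Cost.** A few lines of analysis wording and code, with no change in conduct. The downside is sparse hospital strata, and about 2 points of power for stay if the factors prove not to be prognostic. Fixing the choice in advance also avoids selecting covariates after seeing results.

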### Follow up & data collection

Patients will be seen at 2 and 4 weeks and then at 3 and 6 months post operatively. Follow up data will also be collected at 12 months after surgery. Research staff at the centres will collect the data and submit it to the Trial Office via the EnROL electronic data capture website.

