Analysis of the health economic data will be undertaken separately by those involved in the health economic analysis. Costs will be estimated from the perspective of the UK NHS and health benefits expressed in terms of quality-adjusted life-years (QALYs). The cases where laparoscopic surgery may be considered cost effective will be pre-defined and the mean differential costs and QALYs will be calculated in order to assess whether any of these conditions are satisfied. The relative costs of the operative and peri-operative period will be derived for all trial patients including the cost of consumables that are likely to differ between the two surgical procedures.

QALYs will be calculated for each patient in the trial, on the basis of their responses to the EQ-5D pre-operatively, at one month, three months and six months. Given that the time horizon of the analysis will be less than one year, total costs and QALYs remain undiscounted. To account for the skewed nature of the data, 95% CIs for the differential costs and QALYs will be estimated using bootstrapping methods. Missing data will be imputed using a multivariate multiple imputation procedure (Solas 3.0).

Statistical analysis will be undertaken using Stata (StataCorp LP).

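### The QALY comparison names no adjustment for pre-operative EQ-5D; adjusting would gain precision at no cost, and the absence of an early EQ-5D deserves a stated caveat

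*Protocol article*

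**What the plan says.** The health economics paragraphs of the Analysis section (Protocol article) state that "QALYs will be calculated for each patient in the trial, on the basis of their responses to the EQ-5D pre-operatively, at one month", followed by three and six months. Cost-effectiveness is to be judged against pre-defined conditions: "the mean differential costs and QALYs will be calculated in order to assess whether any of these conditions are satisfied". The 95% intervals come from bootstrapping, and missing data are handled by multiple imputation in named software. No covariate is named for the QALY difference. The economic analysis is assigned to a separate group of analysts.

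Earlier in the same section, physical fatigue is adjusted for its pre-operative level, and the performance indicators are compared by ANCOVA that includes baseline.

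The Randomisation section lists hospital, cancer site and age as minimisation factors. Pre-operative EQ-5D is not among them.

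Table 3 schedules the EQ-5D before surgery (no more than 4 weeks before), at 4 weeks, and at 3 and 6 months. The section on follow-up and data collection says "Patients will be seen at 2 and 4 weeks and then at 3 and 6 months post operatively". The 2-week visit therefore carries no EQ-5D.

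**The concern.** The pre-operative utility is an input to each patient's QALY, and it is likely to be correlated with the later utilities. If the arms differ at baseline by chance, a plain difference in means carries that imbalance in two ways: directly, through the weight on the first time point, and indirectly, through the follow-up values that track it. A regression on baseline takes it out and narrows the interval, using data that are already collected.

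The cost-effectiveness conclusion is drawn from mean differences in costs and QALYs over a six-month horizon, so the precision of the QALY difference matters. The plan states baseline adjustment for other patient outcomes, and without a statement here the separate economic team may not carry it over.

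A smaller matter concerns the schedule. Recovery after surgery is the subject of the trial, and the programme in Table 1 aims for discharge within days. With no utility value between surgery and 4 weeks, a difference confined to that period cannot enter the QALYs.

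**Working it through.** **The plan's own figure.** No QALY figure is stated. The only figure to reproduce is the sample size, which supplies the number per arm.
- Inputs: a difference "of 0.45 standard deviations at p = 0.05 (two-sided"), with 15% loss and 8% conversion.
- 90% power: 2 × ((1.960 + 1.282)/0.45)² = 103.8 per arm. Dividing by (0.85 × 0.92) gives 132.7, so 133 per arm and 266 in total, as stated.
- 80% power: 77.5 per arm. Dividing by (1 − 0.23) gives 100.7, so 101 per arm and 202 in total, as stated. Dividing by (0.85 × 0.92) gives 200.
- After 15% loss, 101 × 0.85 = 85.9, taken as 86 per arm.

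**Assumptions not in the document.** Utility SD 0.2 at every time point; the same correlation r between all pairs of time points, with r from 0.3 to 0.7; area under the curve by the trapezoidal rule (the article names no interpolation).

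**Weights.** With times 0, 28/365.25, 0.25 and 0.5 years, the trapezoid weights are 0.0383, 0.1250, 0.2117 and 0.1250, which sum to 0.5. The pre-operative value carries 0.0383/0.5 = 7.7% of the horizon directly. The three later weights sum to 0.4617.

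**Effect of a chance imbalance.**
- Slope of QALY on baseline: b = 0.0383 + r × 0.4617, which is 0.177, 0.269 and 0.362 for r = 0.3, 0.5 and 0.7.
- SE of the baseline difference: 0.2 × √(2/86) = 0.0305.
- Shift in the QALY difference per one-SE imbalance: 0.0305 × b = 0.0054, 0.0082 and 0.0110.
- With all 101 per arm (SE 0.0281), the range is 0.0050 to 0.0102.
- The shift scales with the SD: at r = 0.5 and 86 per arm it is 0.0062 for SD 0.15 (SE 0.0229) and 0.0103 for SD 0.25 (SE 0.0381).

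**Gain from adjustment.**
- Variance of one patient's QALY: 0.2² × [(1 − r) × Σw² + r × 0.5²], with Σw² = 0.0775.
- At r = 0.5 the bracket is 0.1638, the SD is 0.0809, and the SE of the difference is 0.0809 × √(2/86) = 0.0123.
- Share of variance explained by baseline: b²/bracket = 0.0725/0.1638 = 44%.
- Adjusted SE: 0.0123 × √(1 − 0.44) = 0.0092.
- The same ratio is 0.0313/0.1293 = 24% at r = 0.3 and 0.1307/0.1983 = 66% at r = 0.7. These percentages do not depend on the assumed SD.

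**Early gap (also assumed).**
- A utility gap of 0.1 just after surgery that closes linearly by day 28 is worth 0.5 × 0.1 × 28/365.25 = 0.0038 QALY, none of it recorded. A 2-week form would recover 0.05 × 14/365.25 = 0.0019, about half.
- If the gap closes by day 14, it is worth 0.0019 and a 2-week form records none of it.
- If it starts at 0.2 and is still 0.1 at 4 weeks, the first four weeks are worth 0.15 × 28/365.25 = 0.0115. The schedule captures 0.05 × 28/365.25 = 0.0038, about one third.
- For starting gaps of 0.05 to 0.20 that close in 7 to 28 days, the unrecorded amount is 0.0005 to 0.0077 QALY.

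**The case against.** A reader might infer that the plan commits the analysts to an unadjusted QALY difference. It does not. The article is silent on covariates, a regression-adjusted estimate is also a mean difference that can be bootstrapped, and a separate economic plan may supply the detail. This stands, and it limits the point to an improvement in what is stated. Even so, the article fixes the time points, interval method, discounting and imputation software for this comparison, and it names baseline adjustment for other outcomes, so asking for it here is reasonable.

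A reader might also infer that the unadjusted result would be biased. Under randomisation it is not. A one-SE imbalance shifts the estimate by 0.0082 at r = 0.5, but that variation is already contained in the unadjusted SE of 0.0123, and a valid bootstrap interval reflects it. What is lost is precision, together with protection against an imbalance in the sample that happens to be drawn.

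One could object that the pre-operative form may be completed after randomisation, since surgery may follow randomisation by up to 6 weeks and the form may be up to 4 weeks old at surgery. Patients are blinded over that period, so the score should not depend on arm and remains a proper covariate.

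On the schedule, Table 3 and the Analysis section agree with each other, and early recovery is also covered by hospital stay, 30-day complications and readmission. An extra form would be incomplete, because the sample-size text shows that recruitment had already begun. These objections stand, and they are why the schedule is a secondary point.

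**Conclusion.** The point holds as a free improvement to the analysis. No baseline term is named for the QALY difference, and adding one would remove about 24% to 66% of its variance (44% at r = 0.5, SE 0.0123 to 0.0092). It would also remove a shift of about 0.005 to 0.011 QALY per one-SE chance imbalance. These figures rest on an assumed utility SD of 0.2, equal correlations of 0.3 to 0.7, 86 per arm and a trapezoidal area under the curve.

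A reader might go further and say that these amounts are as large as any plausible QALY difference. The documents do not support that: they give no expected QALY difference, no utility SD and no willingness-to-pay threshold, so whether the cost-effectiveness conclusion would change cannot be judged.

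Nor do they support saying that the early recovery difference is missed altogether. A gap still present at 4 weeks is partly captured, and only one that has closed by then is lost. On an assumed gap of 0.1 closing by day 28, the loss is about 0.004 QALY, roughly a third of the unadjusted SE. The direction is to understate an early benefit. This second matter is real but optional.

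**What to change.** **Main change.** State that the QALY difference will be estimated by regressing QALY on arm, pre-operative EQ-5D and the minimisation factors, fitted within each bootstrap replicate and combined with the planned multiple imputation. The unadjusted difference can be reported beside it. This takes one sentence and no new data; the sample size of 202 is unaffected.

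**Optional change, one of two.**
- Add the EQ-5D to the existing 2-week visit for patients who have not yet reached it, and use it in the area under the curve. The cost is one extra form, an amendment, and missing values for patients already past 2 weeks. It gains nothing if the gap has closed by day 14.
- Keep the schedule, and state in the analysis plan and the report that, with no utility measured between surgery and 4 weeks, the QALY difference may understate an early recovery benefit. This costs nothing.
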